# 8. CRITERIA FOR EVALUATION AND ENDPOINT DEFINITION

## 8.1 Primary Endpoint

The main endpoint of the study will be serum concentrations (nmol/L) of SHBG after 6 months of intervention. We expect to obtain a difference of 15 points comparing the two low dose tamoxifen arms with the two other arms that include lifestyle intervention (step counter), with or without intermittent-caloric restriction^57, 58^. The measurement will be centralized at the Division of Cancer Prevention and Genetics at the IEO.

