## 9.1. Blood

Blood samples for serum biomarkers will be collected at baseline, three and six months, whole blood (EDTA) will be collected only at baseline, whole blood for RNA samples will be collected at baseline and six months.

Blood samples for biomarkers will be drawn under fasting condition (at least 6 hours) preferably between 8 a.m. and 10 a.m. at each visit. A total of 25 ml of blood (5 x 5mL) will be collected into vacuum blood collection tubes containing beads coated with clotting activator for serum separation to be employed for circulating biomarker analysis. Based on specific tubes adopted locally, reference to the manufacture instructions will be followed. blood will be allowed to clot at room temperature for 30 minutes. Then, it will be spun in centrifuge for 10 minutes. Sarstedt Serum Monovettes tubes require 10 min centrifugation at 2000 x g at room temperature, while BD Vacutainer® SST™ and PST™ gel tubes should be spun at a speed of 1300 x g. Swing-out buckets best option for both systems. After centrifugation, the yellow top layer, which corresponds to serum, is pipetted using the disposable transfer pipettes in 6 even aliquots (about 2 mL each) into the polypropylene cryotubes (Thermo Fisher Scientific), specifically labeled according to the Instructions in the Manual of Operations and Procedures. Tubes are tightly capped and stored in a dedicated – 80°C freezer equipped with a temperature control and temperature log chart or an alarm monitoring system per institutional standards.

Moreover, **3 ml whole blood** will be collected in tubes containing EDTA-K2 as anti-coagulant agent. The tube is gently mixed and blood is pipetted using disposable transfer pipettes in 2 even aliquots (about 1.5 mL each) into the polypropylene cryotubes (Thermo Fisher Scientific), specifically labeled according to the Instructions in the Manual of Operations and Procedures. Tubes are tightly capped and stored in a dedicated –80°C freezer equipped with a temperature control and temperature log chart or an alarm monitoring system per institutional standards.

Additionally, **2.5 mL whole blood** will be drawn into PAXgene® Blood RNA Tubes, for immediate stabilization of intracellular RNA, and stored at -20°C to -80°C.

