
## 9.4. Study specimen and procedure management

Planned analysis of circulating and other biomarkers will be determined by specialized laboratories/departments as outlined below:

| **Specimen (amount)** | **Laboratory** |
| --- | --- |

| **Serum: 6 aliquots (2 mL each) per time point**  For all circulating biomarkers  At baseline, 3 months, and 6 months (or study cessation) | [name], PhD  Division of Cancer Prevention and Genetics  European Institute of Oncology |
| --- | --- |
| **Stool: 1 aliquot per time point**  Microbiota analysis at baseline and 6 months  **Whole blood 1 aliquot per time point**  Immune-gene expression profile | Istituto Nazionale Tumori G. Pascale, Naples |
| **Mammograms***  Baseline and final images will be recorded to mammographic analysis | [name] MD  Department of Breast Radiology,  European Institute of Oncology |

*Only in a subgroup of participants

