# 12. STATISTICAL CONSIDERATIONS

## 12.1 Statistical Plan

*Sample size considerations*

Main objective

Given the results found in our previous studies^18, 57^, we considered as main endpoint SHBG (nmol/L) post treatment, which has been shown to be associated with risk of first cancer or cancer recurrence. Taking into account a drop-out rate of 10% we will have to enroll a total of 200 subjects. In fact, a sample size of overall 180 patients (90 per arm) achieves 80% power to detect a difference of 15 points between the null hypothesis that means of SHBG (nmol/L) post treatment are in both arms 70 and the alternative hypothesis that the mean in the tamoxifen arm is 85, with an estimated group standard deviation of 35 and with a significance level (alpha) of 5% using a two-sided two-sample t-test.

Secondary objectives

In order to investigate the effect of caloric restriction on biomarkers, we will subdivide each arm in two further groups: with and without caloric restriction, leading to a 4 arms design (45 patients per arms). Adjusting for multiple testing will be carry out for all secondary objectives that have an explorative nature.

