## 12.3 Statistical analysis

Subject characteristics, information on lifestyle risk factors, diet and serum biomarkers at baseline will be summarized with descriptive characteristics. Median and interquartile range for continuous variables and absolute and relative frequencies for categorical variables will be presented by arms. Kruskal-Wallis test and Chi-square test (Fisher exact test for sparse data) will be used to assess differences at baseline between arms. Comparisons by affected versus high risk subjects of baseline serum biomarkers will be also carried out using Wilcoxon sum-rank test. We will employ linear regression models to investigate the associations between Tamoxifen treatment, LI and ICR with both post-treatment and changes from baseline of SHBG and all serum biomarkers. We will check whether we need to control for confounding factors and the baseline values. The normality of the models’ residuals will be verified by graphically checking the empirical distribution of the residuals and by looking at Q-Q plots, which compare the cumulative distribution of our data with that of the normal distribution. With multivariate logistic regression, serum biomarkers will be also investigated as categorical variables considering different cut-offs.

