
The primary analysis will employ an intention-to-treat approach, which includes all participant irrespective of compliance. An according-to-protocol subgroup analysis will be restricted to women who are “compliant”, such as participants who have taken ≥ 75% of the pills, for thus randomized to tamoxifen and ≥ 75% of the days with the respected caloric restriction, by the reported diary.

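### The stated primary regression uses only women with a 6-month SHBG, about 180 of 200, and gives no role to the 3-month SHBG already collected, so selective loss could bias the LDT effect in either direction

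*Protocol*

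**What the plan says.** **Endpoint.** Section 8.1: "The main endpoint of the study will be serum concentrations (nmol/L) of SHBG after 6 months of intervention".

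**Model.** Section 12.3 relates tamoxifen, LI and ICR by linear regression "with both post-treatment and changes from baseline of SHBG and all serum biomarkers". Baseline adjustment is left open: "We will check whether we need to control for confounding factors and the baseline values". No repeated-measures model or imputation is named for SHBG.

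**Population.** Section 12.3: "The primary analysis will employ an intention-to-treat approach, which includes all participant irrespective of compliance". The next sentence defines the compliant-only analysis.

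**Numbers.** Section 12.1: "a sample size of overall 180 patients (90 per arm) achieves 80% power to detect a difference of 15 points", and "Taking into account a drop-out rate of 10% we will have to enroll a total of 200 subjects".

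**Samples.** Section 9.1: "Blood samples for serum biomarkers will be collected at baseline, three and six months". The serum row of the specimen table in section 9.4 reads "At baseline, 3 months, and 6 months (or study cessation".

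**Leaving.** Section 7.7 keeps women who stop the assigned intervention in follow-up, where possible, to obtain endpoint data. Section 7.8 allows a woman to go off study for, among other reasons, an adverse event or non-compliance.

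**The concern.** A regression on a single 6-month value omits every woman who lacks that value unless something is added to keep her in. The protocol plans for about 20 such women. For those who leave after the 3-month visit, SHBG at baseline and 3 months will already have been drawn. Section 2.3 describes an earlier low-dose tamoxifen study in which the SHBG rise was seen at 3 months and was stable at 6 and 12. It adds that only the estradiol/SHBG ratio was published. The 3-month value may therefore carry real information about the missing 6-month value, and the primary model makes no use of it.

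What is at stake is the LDT versus LI contrast. If the women without a 6-month value responded differently from those who stay, and this differs between arms, the contrast among women with the value is not the contrast among all women randomised.

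**Working it through.** **1. The plan's own figures.** Inputs from section 12.1: means 70 and 85, SD 35, two-sided 5%, 90 per pooled arm.
- Power, exact two-sample t-test: 81.6% (normal approximation 82.0%), consistent with the stated 80%.
- Enrolment: 180 / (1 − 0.10) = 200, as stated.
- The power calculation therefore rests on 180 women with a 6-month value out of 200 randomised.

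**2. Size by hand.** Let d be the fraction missing in an arm, m the mean they would have had, and 85 (LDT) or 70 (LI) the mean among women with a value. The all-randomised mean is (1 − d) × observed mean + d × m. The contrast among women with a value is 15 throughout. The values of d by arm and of m are assumptions; the protocol gives only 10% overall.

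| Missing LDT / LI | Means of missing LDT / LI | All-randomised difference | Completer bias |
|---|---|---|---|
| 10% / 10% | 70 / 70 | 83.5 − 70 = 13.5 | +1.5 |
| 15% / 5% | 70 / 70 | 82.75 − 70 = 12.75 | +2.25 |
| 10% / 10% | 70 / 55 | 83.5 − 68.5 = 15.0 | 0 |
| 10% / 10% | 85 / 55 | 85 − 68.5 = 16.5 | −1.5 |
| 5% / 15% | 70 / 55 | 84.25 − 67.75 = 16.5 | −1.5 |

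The sign depends on which women are missing.

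**3. Does the 3-month value help?** Simulation with 100 women per pooled arm, SD 35 and a true difference of 15 at 3 and 6 months. Assumed correlations are 0.6 (baseline with either later visit) and 0.8 (3 with 6 months). All loss falls after the 3-month visit and is more likely after a poor baseline-to-3-month rise. Using month 3 means predicting the missing 6-month value from arm, baseline and 3-month SHBG, as a stand-in for a likelihood-based longitudinal model.

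| Loss LDT / LI | Completers, baseline-adjusted | Completers, unadjusted | Using month 3 |
|---|---|---|---|
| 15% / 5%, related to response | 16.7 to 17.5 | 15.7 to 16.2 | 15.0 |
| 5% / 15%, related to response | about 13.3 | smaller bias | about 15 |
| 10% / 10%, same relation in both arms | 15.0 | about 15 | about 15 |
| 15% / 5%, unrelated to SHBG | 15.0 | about 15 | about 15 |

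The ranges reflect how strongly loss is tied to response. Relative to 15, the adjusted bias is (16.7 − 15)/15 = +11% to (17.5 − 15)/15 = +17%, or (13.3 − 15)/15 = −11%.

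**4. Equal rates, different mechanism.** With 10% lost in each arm and correlations of 0.6 to 0.85, response-related loss in LDT only gives an adjusted 16.4 to 16.6. In LI only it gives 13.4 to 13.7. Using month 3 gives 15.0 to 15.1 in both cases. Unevenness can thus lie in the rate or in the reason for loss.

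**5. Precision.** When loss is random and equal, the standard error falls from 4.23 to 4.13: (4.23 − 4.13)/4.23 = 2.4%.

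**The case against.** **Missing-data rules are often left to a SAP.** No complete-case rule is written, and a SAP that is not shown may deal with missing values. This stands as a caution. But the protocol itself names the model, the endpoint time and the evaluable number, and together they describe an analysis of women with a 6-month value.

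**The intention-to-treat sentence.** A reader might infer that it is contradicted, because not all women would be analysed. The documents do not support that. The sentence concerns compliance and is set against the compliant-only analysis; it does not promise complete outcome data. Inflating 180 to 200 for drop-out is ordinary planning.

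**Stopping is not the same as missing.** Section 7.7 keeps women who stop the intervention in endpoint follow-up where possible, so fewer than 20 may lack the value. This stands, but section 7.8 still allows exit for adverse events or non-compliance.

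**Direction.** A reader might infer that side effects will thin out the LDT arms and inflate the LDT effect. Section 2.2 reports more menopausal symptoms on tamoxifen. Against that, section 2.1 cites low discontinuation on LDT, section 2.4 calls its side effects only marginally greater than on placebo, and sections 2.4 and 10.1 list side effects of ICR, which is given in one LDT arm and one LI arm. Nothing links side effects to a poor SHBG rise. An upward bias is possible but not established.

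**Cessation samples.** A reader might infer from section 9.4 that a cessation sample replaces the 6-month value. That section is a specimen table and says only when serum is taken. Its analytic use is unstated.

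**Limited gain.** The 3-month SHBG is not unused in the trial, since change in SHBG over time is a secondary endpoint (section 8.2). The precision gain is small, and women lost before month 3 have no 3-month value. All of this is correct.

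**Conclusion.** The point holds as a weakness of the stated primary method. A 6-month regression uses about 180 of 200 women and makes no use of the 3-month SHBG. If loss is uneven by arm, in rate or in mechanism, and related to early response, the LDT effect is biased up or down. In the 15%/5% scenario and its reverse, the baseline-adjusted bias is roughly 1.7 to 2.5 nmol/L in size against a true 15; the unadjusted bias is smaller. It is nil if loss is random, or equal and with the same relation to response in both arms.

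These sizes rest on assumed correlations, an assumed split of drop-out and loss after the 3-month visit. The month-3 value removes the bias here because loss was made to depend on observed SHBG; loss driven by unobserved values would not be fully corrected. The change is worth making because it is cheap and protects in both directions, not because an overstated LDT effect has been shown.

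**What to change.** Make the primary analysis a longitudinal model (constrained-baseline or MMRM) of SHBG at baseline, 3 and 6 months. Include all randomised women with any SHBG value, use centre and disease status as covariates, and take the LDT versus LI contrast at month 6 as the primary estimate. This also settles the open question of baseline adjustment.

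State that a study-cessation sample is analysed at its actual time and is not treated as month 6. Reconcile sections 7.7 and 7.8 so that it is clear when a woman who is non-compliant or has an adverse event still gives 6-month serum. A sensitivity analysis giving missing LDT women LI-like values would cover loss that observed SHBG does not explain.

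Cost: wording and slightly more programming; the samples are already planned. Downside: when loss is random the gain is only about 2% in standard error, and women lost before month 3 contribute only their baseline value.

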# 3. STUDY DESIGN

The TOLERANT (Low dose **T**am**O**xifen and **L**if**E**style changes for b**R**east c**AN**cer preven**T**ion) study is a randomized four-arm phase II intervention trial that will enroll 200 participants at high risk of breast cancer in four Italian centers (Milan, Genoa, Padua and Naples).

Potentially eligible women will be informed about the study and will provide signed informed consent before participation. At baseline, participants will be screened to confirm eligibility and will be randomly assigned (1:1:1:1) to one of the four intervention arms (Figure 1):

*Arm 1:* Low dose Tamoxifen (LDT) i.e 10 mg every other day;

*Arm 2:* Low dose Tamoxifen (LDT) + Intermittent Caloric Restriction (ICR);

*Arm 3:* Lifestyle intervention (LI) using a step counter;

*Arm 4:* Lifestyle intervention (LI) using a step counter + Intermittent Caloric Restriction (ICR).

Figure 1

[figure not shown]

Stratification: center and disease status (high risk vs previous IEN)

A schematic description of the study procedures is reported in figure 2.

Figure 2

[figure not shown]

Trained staff including dietitians/nutritionists will provide advices based on international and national recommendations (WCRF.2018; CREA, 2019 https://www.crea.gov.it/web/alimenti-e-nutrizione/-/linee-guida-per-una-sana-alimentazione-2018) at baseline to all participants. Depending on intervention allocation, dietitians/nutritionists will provide a caloric restriction plan to Arm 2 and 4. Participants included in Arm 3 and 4, will receive a step counter that encourages both increased physical activity and decreased sedentary time. Depending on intervention allocation, tamoxifen pills will be provided (Arm 1 and 2). All participants will receive a calendar in order to record drug intake, ICR dates and weekly step counter where appropriate. The study interventions will last 6 months.

To maintain high compliance during the 6-month intervention phase (T2, T3 and T5) participants will receive phone calls in order to monitor and reinforce adherence to the proposed intervention, and to record possible adverse effects. At visit T1, T4 and T6 blood samples will be collected, anthropometric measures, study questionnaires will be collected. Stool will be collected at T1 and T6. Depending on local availability, a sub-sample of participants will be invited to do DEXA for adipose tissue evaluation.

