We will propose the so-called “5:2 diet,” with 5 days/week at regular energy intake and 2 days/week at an ∼75% energy deficit (the diet will be restricted at 500-700 Kcal per day, corresponding to a 75% reduction compared to normal intake). Detailed personalized meal plans will be created for each participant, in which portion sizes are reported and possible choices for meal components arranged by food groups to meet the target caloric amount foresee. Participants will receive a leaflet containing dietary advice and physical activity recommendations to be followed for the study period. During the 2 days of energy restriction, a daily intake of a minimum of 2 L of liquids (water, tea or infusions) will be strongly recommended to avoid dehydration and side effects of fasting such as hunger and lightheadedness, increased cold sensitivity, weakness and headaches. Trained dietitians/nutritionists will provide personal nutrition consultations at baseline and during the study period. The intervention will be monitored and reinforced by phone call at month 1, 2 and 5, and to monitor possible side effects. The first personal consultation within the first month will be used to motivate participants, to monitor compliance, and to consolidate knowledge about dietary programs proposed. Participants will be instructed to complete a fasting diary to monitor the frequency of energy-restricted days. During the 2 days of ICR, women will be advised to avoid tiring and particularly intense activities. If women are used to practice sport, it will be suggested to walk or practice yoga, meditation and light pilates sessions.

Lifestyle intervention

Participants will receive personalized advice on healthy lifestyle and the use of a step counter device. These devices tend to encourage both increased physical activity and decreased sedentary time. They are able to record total steps taken, total distance traveled, total time active during the day and the greatest length of time of consistent movements done during the day. A goal of "10.000 steps" per day has been widely promoted and advocated as a strategy for increasing physical activity among able adults. Participants will be asked to wear the step counter during the 6-month intervention period. They could use a smartphone or a tablet application to get feedback on their activity and sedentary time.

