## 5.5 Adherence/Compliance

To be compliant, a participant has to take ≥ 75% of the scheduled pills and/or follow 75% of the expected days of intermittent caloric restriction as per assigned arm. We propose the use of multiple methods of adherence monitoring: subject self-reporting, diary completion and tablets count.

*Diary completion*: All participants will receive at each visit a calendar to facilitate tracking and recording of protocol treatment (Appendix C). Each participant will be asked to mark or write Yes/No in the corresponding day of the diary. Based on treatment assignment, participants are asked to fill the diary and some additional space will be left for participant’s notes.

A total of 120 pills will be supplied in Arms 1 and 2. Each participant will be asked to return all full and empty blisters.

Should the tablets not be returned, compliance will be calculated from the diary only.

Participants on Arms 2 and 4 will be asked to mark yes/no in the corresponding dates of ICR.

Participants on Arms 3 and 4 will be asked to record the step count number on a weekly basis.

An according-to-protocol subgroup analysis will be restricted to women who are “compliant”, such as participants who have taken ≥ 75% of the pills, for those randomized to tamoxifen and ≥ 75% of the days with the respected caloric restriction, by the reported diary

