**SCHEDULE OF EVENTS**

| Evaluation/ Procedure | T0  Screening Visit  Days -30-1 | T1  Baseline Visit/Randomization  Day 0 | T2  Phone call/ teleconsulting  (within 1 month) | T3  Phone call/ teleconsulting  (2 months) | T4  Visit  (3 months) | T5  Phone call/ teleconsulting  (5 months) | T6  Final Visit  (6 months) |
| --- | --- | --- | --- | --- | --- | --- | --- |
| Informed Consent | X |  |  |  |  |  |  |
| Stool Collection kit | X |  |  |  | X |  |  |
| Assess eligibility | X | X |  |  |  |  |  |
| Medical history |  | X |  |  |  |  |  |
| Physical exam/ anthropometric measures and body composition (BIVA) |  | X |  |  | X |  | X |
| Tobacco/alcohol use assessment |  | X |  |  |  |  |  |
| Fasting blood collection^a-b^ |  | X^b^ |  |  | X |  | X^b^ |
| Gravindex |  | X* |  |  |  |  |  |
| Stool collection |  | X |  |  |  |  | X |
| Mammography (according to Institutional guidelines)^c^ |  | X |  |  |  |  | X |
| Body fat composition (DEXA)^d^ |  | X |  |  |  |  | X |
| Concomitant medications |  | X |  |  | X |  | X |
| Baseline Symptoms |  | X |  |  |  |  |  |
| Randomization |  | X |  |  |  |  |  |
| Nutrition counseling |  | Arms 2, 4 only | Arms 2, 4 only | Arms 2, 4 only | Arms 2, 4 only | Arms 2, 4 only |  |
| Physical activity counseling |  | Arms 3, 4 only | Arms 3, 4 only | Arms 3, 4 only | Arms 3, 4 only | Arms 3, 4 only |  |
| Tamoxifen safety |  |  | Arms 1, 2 only | Arms 1, 2 only | Arms 1, 2 only | Arms 1, 2 only | Arm 1, 2 only |
| WCRF recommendations | X | X |  |  |  |  |  |
| Collect study agent |  |  |  |  |  |  | X |
| Compliance |  |  | X^g^ | X^g^ | X^e^ | X^g^ | X^e^ |
| Review diary |  |  |  |  | X |  | X |
| Adverse events |  |  | X | X | X | X | X |
| Study Questionnaires: QoL, DIET and IPAQ | X^f^ | X |  |  | X |  | X |

* In women of childbearing potential only

a. Glycemia will be measured locally and blood specimen will be collected for biomarkers as per Manual of procedure

b. Additional blood collection in dedicated tubes for RNA extraction as per Manual of procedure.

c. Mammogram will be performed only in a subgroup of participants based on their age and center guideline, and can be within 6 or 12 months from baseline visit depending on disease status.

d. In a subgroup of participants only, depending on local availability.

e. Revision of diary completion only. Unused and/or empty blisters will be returned at month 6 visit arms 1,2

f. 3-day food records only

g. Compliance with Intermittent Caloric Restriction

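### The according-to-protocol rule has no adherence criterion for the lifestyle intervention, so the supplementary tamoxifen versus lifestyle contrast filters only the tamoxifen side on its own assigned intervention

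*Protocol*

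**What the plan says.** Section 5.5 defines a compliant participant as one who must "take ≥ 75% of the scheduled pills and/or follow 75% of the expected days of intermittent caloric restriction as per assigned arm". Section 12.3 then defines the analysis set: "An according-to-protocol subgroup analysis will be restricted to women who are “compliant”, such as participants". It names as compliant the "participants who have taken ≥ 75% of the pills, for thus randomized to tamoxifen and ≥ 75% of the days" of caloric restriction, as reported in the diary. Section 5.5 ends with almost the same sentence.

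Arm 3 is described in section 3 as "Lifestyle intervention (LI) using a step counter" and nothing else; Arm 4 adds ICR. Section 5.1 says of the device: "Participants will be asked to wear the step counter during the 6-month intervention period". Section 5.5 adds: "Participants on Arms 3 and 4 will be asked to record the step count number on a weekly basis". No threshold is attached to that record. In the Schedule of Events, the compliance entry at the three phone contacts is footnoted "Compliance with Intermittent Caloric Restriction". At the two clinic visits the footnote names diary review and blister return.

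The schema gives the main aim as Arms 1 and 2 against Arms 3 and 4. Section 12.3 makes the intention-to-treat analysis primary.

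**The concern.** In a per-protocol comparison of two active strategies, each side should be held to its own assigned intervention. Here tamoxifen women who stop their pills leave the set, including those who stop because of toxicity. LI women who stop wearing the counter stay in. What separates adherers from non-adherers is thus selected for differently on the two sides of the main contrast.

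The Background (section 2) itself says that SHBG responds to diet and physical activity. Women who do not follow LI but are kept could dilute the LI effect and make the tamoxifen advantage look larger. That direction is plausible but cannot be shown from the protocol. What is at stake is the reading of the supplementary analysis as an effect in compliers.

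**Working it through.** **1. The plan's own figures.** The protocol gives no according-to-protocol sample size. Its design figures (section 12.1) are a difference of 15 nmol/L, SD 35, two-sided 5% and 90 per pooled group. The noncentrality is 15 / (35 × √(2/90)) = 2.875. The t-test power is 81.6%, which agrees with the stated 80%, and 180 / 0.90 = 200. The design reproduces and does not depend on the compliance rule.

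**2. The rule applied arm by arm**, using the section 5.5 wording that the criteria follow the assigned arm.

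| Arm | Assigned | Pill filter | ICR filter | LI filter |
| --- | --- | --- | --- | --- |
| 1 | tamoxifen | yes | not applicable | not applicable |
| 2 | tamoxifen + ICR | yes | yes | not applicable |
| 3 | LI | not applicable | not applicable | none |
| 4 | LI + ICR | not applicable | yes | none |

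The ICR filter falls on one arm of each side. The pill filter falls on both tamoxifen arms, and nothing on the LI side corresponds to it. In Arm 1 versus Arm 3 the imbalance is complete.

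**3. Size under assumed compliance.** Let p be the proportion meeting the pill criterion and q the proportion meeting the ICR criterion. Both are assumptions, taken as independent and as equal across the arms where they apply. With 50 randomized per arm:

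- Tamoxifen side: 50p + 50pq = 50p(1 + q)
- LI side: 50 + 50q = 50(1 + q)
- Ratio of the two sides: p

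The ICR term cancels, so under these assumptions the difference in retention comes wholly from the pill filter.

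| p / q | Arm 1 | Arm 2 | Arm 3 | Arm 4 | Tamoxifen vs LI |
| --- | --- | --- | --- | --- | --- |
| 90% / 80% | 45 | 36 | 50 | 40 | 81 vs 90 |
| 85% / 70% | 42.5 | 29.75 | 50 | 35 | about 72 vs 85 |
| 80% / 60% | 40 | 24 | 50 | 30 | 64 vs 80 |

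**4. With the planned 10% drop-out** (45 per arm) the first and last rows become 72.9 vs 81.0 and 57.6 vs 72.0. Arm 3 keeps all 45 and makes up 45/81 = 56% to 45/72 = 63% of the LI group. More than half of the comparator then passes no adherence filter at all.

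**5. Pill wording.** At one tablet every other day, 6 months (180 to 184 days) means 90 to 92 scheduled pills, and 75% of these is 68 to 69. The opening of section 5.5 refers to scheduled pills and expected days. The two sentences that define the analysis set drop both adjectives.

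**The case against.** Four points can be made for the plan.

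- **The list is open and a SAP may complete it.** The phrase introducing the criteria in 12.3 is not exhaustive. But the protocol states the rule twice with numerical thresholds, and the definition at the start of 5.5 is not open-ended. As written the rule is asymmetric, and an LI criterion added later would not be prespecified here.
- **The analysis is supplementary.** This stands, and it limits the importance of the point.
- **Any per-protocol analysis is exposed to selection on adherence.** Also true, and an LI criterion would not remove it. It would put a filter on both sides.
- **Recording steps measures diary completion more than LI adherence.** This stands too: a woman who records low counts every week would pass. Such a criterion is a minimum measure of device use.

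Two stronger readings are tempting. A reader might infer that compliant tamoxifen women are compared with all LI women, so that selection is on one side only. The documents do not support this, because Arm 4 must meet the ICR-day rule, just as Arm 2 must.

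A reader might also take the supplied quantity as the pill denominator, since "A total of 120 pills will be supplied in Arms 1 and 2". Then 0.75 × 120 = 90 pills, or 98% to 100% of the 90 to 92 scheduled. But 5.5 opens with scheduled pills, the analysis sentences refer back to the compliant women defined there, and 120 is nowhere used as a denominator. Only the wording needs aligning.

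**Conclusion.** The point holds as a fault in a stated rule. The according-to-protocol contrast of Arms 1+2 against 3+4 selects tamoxifen women on adherence to tamoxifen but never selects LI women on adherence to LI. It cannot be presented as an effect in compliers. That conclusion follows from the text and needs no assumption.

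The retention figures, 81 vs 90 to 64 vs 80, are illustrative. They rest on assumed, independent compliance rates and on 50 per arm before drop-out. They show the imbalance in numbers, not the size or direction of any bias in SHBG. The primary intention-to-treat result and the sample size stand. The rule should be corrected, but it does not threaten the trial's main conclusion.

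**What to change.** In sections 5.5 and 12.3, state the set arm by arm and add a prespecified LI adherence criterion for Arms 3 and 4 from the weekly step record already collected. One example is a step count recorded in at least 75% of the 26 weeks (0.75 × 26 = 19.5, so 20 weeks), described as a minimum measure of device use. In Arm 4 require it together with the ICR criterion.

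If no LI criterion is adopted, say that LI adherence is not assessed and that the result is not a complier comparison.

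As a wording alignment only, carry scheduled pills and expected days from the opening of 5.5 into the analysis-set sentences of 5.5 and 12.3.

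The cost is wording in two sections, no new data, and a somewhat smaller LI set. For example, if an assumed 90% of LI women met the criterion and 80% met the ICR rule, independently, the LI side would fall from 90 to 50 × 0.9 + 50 × 0.9 × 0.8 = 81. At 80% and 60% it would fall from 80 to 50 × 0.8 + 50 × 0.8 × 0.6 = 64.
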